Box 2Summary of key features of the Picking up Hidden Osteoporosis Effectively during Normal CT Imaging without additional X-rays (PHOENIX) study protocolPragmatic featuresPatients attending CT waiting rooms are offered a PHOENIX invitation pack comprising a novel informed consent form/data capture tool to ascertain Fracture Risk Assessment (FRAX) score (online supplemental file 1) that the patient can fill out with or without assistanceThe intervention (tested in group 1) comprises (i) retrieving the CT scans of those ‘amber’ or ‘red’ risk individuals with moderate to high 10-year fracture risk by FRAX, (ii) hip and spine bone mineral density analysis with vertebral fracture assessment and (iii) sending the general practitioner (GP) guidance from a clinical decision tree.The intervention take place ‘behind the scenes’ without impacting on patient flow or the radiography/radiology workflow.Data (imaging, clinical risk factor, Patient Identifiable Information (PID) including sensitive clinical information) flow via secure encrypted and approved methods including the NHS Image Exchange Portal, Picture Archiving and Communications System (PACS) and nhs.net secure clinical email.Technical staff can ‘pull’ clinical CT images for assessment at any time.Primary outcome measures/end pointsFeasibility of recruitment: defined as ability to randomise 375 ‘at-risk’ participants over continuous 10-month period.Retention: defined as retaining 75% of surviving participants to 12 months postrandomisation, proven by receipt of follow-up postal questionnaire (specifically an answer to the bone active medication received; yes/no question).Secondary outcome measures/end pointsNew vertebral fracture identification across three arms assessed at 12 months.Osteoporosis identification across three arms assessed at 12 months.Bone active medication initiation across the three arms assessed at 12 months.Survival at 12 months across three arms assessed at 12 months.Inclusion criteria: participants eligible for the trial should fulfil all of the following at randomisation:Attending for a routine clinical CT scan.Able to provide informed consent.Aged ≥65–90 years (women) or ≥75–90 years (men) attending for CT for any clinical reason, where the spine and/or hips are visible in scan images.Exclusion criteriaMetalwork in hips (due to streak artefact on the contralateral hip within CT).Known to be receiving prescription treatment for osteoporosis other than calcium/vitamin D (ie, bisphosphonate drug, strontium ranelate, denosumab, raloxifene or teriparatide since it would be futile to identify already known and treated osteoporosis).Prone CT scan (which cannot currently be processed by the software).Role of patients and the publicActively participated in the study design in focus groups within the project team.Assisted in the design of data collection tools, including the informed consent form and information leaflet.Provided guidance on the acceptability of approaching participants in CT scan areas and insight into the anxiety of attending hospital among some more elderly members of society. Adding country of origin and ethnicity questions to consent form to facilitate FRAX.Impact of COVID-19 pandemicRecruitment had to be paused due to the COVID-19 pandemic, then restarted in just one centre without face-to-face contact with patients. Therefore, recruitment was either by clinical approach/discussion versus self-consent based on just handing out recruitment packs after COVID-19 restrictions were brought in.

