
10.1136/bmjopen-2021-050343.supp1Supplementary data

The PHOENIX study is a parallel three-group, non-blinded randomised controlled study of volunteers aged ≥65–90 years (women) or ≥75–90 years (men) attending for CT for any clinical reason, where the spine and/or hips are visible in scan images. Specifically, CT-attending patient volunteers who have an elevated 10-year fracture risk (within the amber or red zones of the UK FRAX graphical outputs for further action) are randomised to one of three groups. The three arms allow comparison between (1) the PHOENIX intervention, (2) an alternative active control ‘middle’ group (to assess whether GPs will investigate or treat patients based solely on receipt of a populated FRAX questionnaire) and (3) a control (‘usual care’) group where no action is taken. Potential participants are identified ahead of attendance by the clinical or research team reviewing CT lists. Those eligible by age, sex and region of the body being scanned are handed the PHOENIX pack while attending the CT department. The specially designed informed consent form (online supplemental file 1) first guides the potential participant through eligibility screening questions (*Do you take medication for your bones once a week that requires you to sit or stand upright? Do you have a yearly infusion (drip) or injection for your bones? Do you have a hip replacement? Have you ever had a hip operation?*). If there is an affirmative answer to any of these questions, individuals are asked to return their forms and go no further. Those individuals who answer ‘no’ to all the questions are asked to supply key demographic data: date of birth, height, weight, country of origin and ethnicity (needed for accurate FRAX calculation) and National Health Service number (receptionists support the patient as needed with the latter). Individuals are also asked to document the reason for their scan, if they know it.

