### Statistical analysis

Daily screening logs will be kept determining: (i) the total number of days (n) where patients were approached in each centre and (ii) the daily totals of PHOENIX invitation packs distributed. This log will also record if a numbered pack was not given out on a day (eg, if the patient did not arrive for scanning, or the receptionists omitted to give out the pack). The total number of consented individuals (x) as well as the number of consented individuals per day (total x/n overall, and per centre) will be calculated. The number of consented but subsequently excluded individuals (y) will be kept (eg, for subsequently discovered metalwork in the scan, technical issues with scan). The number of randomised participants will be calculated (z=x−y), and the rate of randomisation (z/n overall, and per centre). These data will be captured from screening logs and entered manually onto a database. The REDCap database will be used to record details of all consenting patients (z). The database will be locked on completion of data entry and when missing data or any discrepancies are resolved. The data will be exported for statistical analysis to the study statisticians with assistance from the chief investigator.

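### The medication questions on the consent form are narrower than the drug-treatment exclusion, so some patients already on treatment can be randomised and might be counted as having started treatment

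*Protocol article*

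**What the plan says.** The exclusion criteria in Box 2 (Methods and analysis) rule out patients "Known to be receiving prescription treatment for osteoporosis other than calcium/vitamin D (ie, bisphosphonate drug, strontium ranelate, denosumab, raloxifene or teriparatide"). The reason given there is that finding osteoporosis already known and treated would be futile. The criterion sets no condition on how often or by what route the drug is taken.

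Methods and analysis then lists the screening questions on the consent form. Two concern medication: "Do you take medication for your bones once a week that requires you to sit or stand upright" and "Do you have a yearly infusion (drip) or injection for your bones". The other two concern hip replacement and hip surgery. The rule attached to them is "If there is an affirmative answer to any of these questions, individuals are asked to return their forms and go no further". Those who answer no throughout go on to the demographic and FRAX questions and, if in the amber or red zone, to randomisation.

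Two other eligibility steps are described. Before the pack is given out, "Those eligible by age, sex and region of the body being scanned are handed the PHOENIX pack while attending the CT department". After consent, the Statistical analysis section allows later exclusions, with the examples "for subsequently discovered metalwork in the scan, technical issues with scan".

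The relevant secondary outcome in Box 2 is "Bone active medication initiation across the three arms assessed at 12 months". The article describes one 12-month treatment item, a yes/no question on whether bone active medication was received. It appears in the definition of the retention outcome.

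**The concern.** The screen does not reach everyone the exclusion names. A person on a listed oral drug taken other than once a week can answer every question truthfully and still enter the trial. If the word yearly in the second question governs injection as well as infusion, the same holds for injections given on any other schedule. The form can be completed without assistance, and after COVID-19 restrictions packs were simply handed out, so nobody need be present to ask a follow-up question.

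Two things are at stake. First, patients the protocol means to exclude would count towards the co-primary target of 375 randomised. Second, the outcome is the start of treatment, whereas the one item described records receipt. If that item alone fed the outcome, continuing users would look like new starters. Methods and analysis says this outcome will inform power calculations for any future trial, so an inflated usual-care rate would carry forward.

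**Working it through.** **Criterion against screen**

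| Patient on a listed drug | Excluded by Box 2? | Stopped by the form? |
|---|---|---|
| Oral, once weekly, taken upright | Yes, if known | Yes |
| Oral, any other schedule | Yes, if known | No |
| Yearly infusion or injection | Yes, if known | Yes |
| Injection on another schedule | Yes, if known | Only if injection is read without yearly |
| Infusion on another schedule | Yes, if known | No |

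The check before the pack is handed out names age, sex and scanned region. The post-consent examples name metalwork and technical problems. The baseline questionnaire is described as covering quality of life and resource use. None of these names medication.

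**The plan's own power**

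Inputs from Power for treatment proportions: 4.5%, 15.5% and 20.3% (usual care, FRAX to GP, PHOENIX), 375 randomised 1:1:1, two-sided 5%.

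For a trend test with scores 0, 1, 2 and n per arm:
- p̄ = (0.045 + 0.155 + 0.203)/3 = 0.1343
- numerator = n(p₃ − p₁) = 125 × 0.158 = 19.75
- null variance = 2n·p̄(1 − p̄) = 29.07
- alternative variance = n[p₁(1 − p₁) + p₃(1 − p₃)] = 25.60
- power = Φ[(19.75 − 1.96√29.07)/√25.60] = 96.5%

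The article states 96%. The 2-df chi-square approximation gives 93.0%, against a stated 93%. At 280 the approximations are 90.1% (trend) and 83.6% (2-df), against a stated figure above 84%. The plan's figures therefore reproduce, the last to within half a point for the 2-df test.

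**If existing users were counted as events**

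Let f be the share of randomised patients already on treatment. The article does not give f, so 2% and 5% are assumptions. If all of them answer yes at 12 months and the rest start treatment at rate p, the observed rate is f + (1 − f)p. Each arm rises by f(1 − p), which is most where p is lowest.

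- f = 2%: increments 1.9/1.7/1.6 points, rates 6.4/17.2/21.9%
- f = 5%: increments 4.8/4.2/4.0 points, rates 9.3/19.7/24.3%

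The gap between PHOENIX and usual care goes from 15.8 to 15.5 or 15.0 points, and the ratio from 4.5 to 3.4 or 2.6. The usual-care rate rises by a factor of 6.41/4.5 = 1.42 or 9.275/4.5 = 2.06.

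Simulated power (400,000 trials per cell):

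| f | Trend, 125/arm | Trend, 93/arm | 2-df, 125/arm | 2-df, 93/arm |
|---|---|---|---|---|
| 0 | 97.3% | 91.3% | 96.6% | 89.2% |
| 2% | 94.5% | 86.1% | 92.6% | 82.2% |
| 5% | 89.0% | 78.0% | 85.2% | 72.1% |

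The trend approximation above gives 96.5/93.7/88.4% at 375 and 90.1/85.2/77.5% at 280, which is the same pattern.

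**Effect on the recruitment count**

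375 × 0.02 = 7.5 and 375 × 0.05 = 18.75, so about 8 or 19 of the 375 would be existing users.

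**The case against.** The strongest reply concerns the outcome. A reader might infer that existing users will be counted as treated at 12 months. The article does not support that. It describes the outcome as initiation in Box 2, and as treatment commenced in Methods and analysis. The yes/no wording serves to show which answer proves retention. The questionnaires are not shown and may record prior use or start dates. This objection stands: miscounting is possible, not established, and the rates and power above are conditional on it.

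A reader might also suppose that existing users lift every arm equally. They do not: the increment is f(1 − p), and with equal increments the absolute differences would not change at all. Nor does the error favour an arm, since randomisation spreads existing users evenly on average.

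Three further points have some force. The criterion says known to be receiving, so an undetected user is not strictly a breach; yet the form is the only means of knowing that the article describes. The second question can be read as covering any injection, which narrows the gap but leaves the oral drugs. The post-consent exclusions are only examples, and staff review CT lists beforehand, so a medication check may exist in practice; none is described.

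Finally, this is a secondary outcome of a feasibility study. The retention co-primary needs an answer, whether yes or no, and is unaffected.

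**Conclusion.** The mismatch between exclusion and screening questions stands on the text alone. Users of listed oral drugs on schedules other than weekly, and possibly users of non-yearly injections, can pass the described screen, be randomised and count towards the 375.

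The effect on the treatment outcome is conditional on two things that the article does not settle: how many such patients enter, and whether initiation is derived without treatment status at baseline. If both go badly, the absolute contrast barely moves (under one point at f = 5%). The main damage is to the usual-care rate, which would about double at 5%, with a loss of trend power of 8 points at full size and 13 points after maximum attrition. At f = 2% the trend test still exceeds the 84% stated for 280 participants. The point deserves correction because the repair is cheap and the rates are meant to inform the next trial.

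**What to change.** Reconcile Box 2 with the consent form. Reword the medication item so that it asks about every prescription osteoporosis drug in the exclusion, whatever its schedule or route, with the drug names listed.

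State that initiation means treatment started after randomisation. If the questionnaires do not already capture this, add one item on prior use at the time of the CT scan, or a start date. Keep any existing users in their randomised arm as not initiated, in line with the intention-to-treat analysis, and add a sensitivity analysis that leaves them out of all arms.

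The cost is a minor form amendment and slightly more questionnaire burden. If recruitment has finished, only the follow-up item and the derivation of the outcome need to change.

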**Figure 1 F1:**
[figure not shown]
Study flow chart for the Picking up Hidden Osteoporosis Effectively during Normal CT Imaging without additional X-rays (PHOENIX) study. BMD, bone mineral density; GP, general practitioner; FRAX, Fracture Risk Assessment; VFA, vertebral fracture assessment; MSK, Musculoskeletal.

### Group 1

The PHOENIX intervention. In brief, bone health for the red/amber risk participant is assessed using the CT images already captured, with computer-aided diagnosis of vertebral fractures performed by one of two trained NHS and accredited bone density technicians using Mindways QCT Pro (Mindways, Austin, Texas, USA) in Cambridge. The output is a consultant clinician-verified report (figure 2) sent to the GP with details of (i) femoral neck and/or spine bone density results, (ii) vertebral fracture diagnosis (yes/no/level affected), (iii) FRAX estimated 10-year risk of major osteoporotic fracture, (iv) any recommended follow-up investigations and a (v) simple treat/do not treat decision based on National Osteoporosis Guideline Group (NOGG) intervention thresholds, with a suggestion of specific treatments recommended by NICE guidelines (the decision tree is shown in online supplemental file 2). These steps can take place at any time after the patient has gone home from having their CT. Any CT scanner to be used for CT densitometry must be calibrated by reference to a QCT phantom and recalibrated in the event of any X-ray tube change. The technical aspects of the PHOENIX intervention done at study entry in group 1 (and at study exit in the others two groups) are as follows: all analysis is conducted within the Mindways QCT Pro software tool using one of two standalone hospital-connected PCs as illustrated by screenshots (figure 3). Technical steps involved in the full PHOENIX intervention are mentioned in box 3.

10.1136/bmjopen-2021-050343.supp2Supplementary data

Box 3The Picking up Hidden Osteoporosis Effectively during Normal CT Imaging without additional X-rays (PHOENIX) intervention (group 1): technical and practical stepsCT scan retrieved via PACS into Mindways via its DICOM transfer tool (Cambridge) or in the case of the spoke sites, via the UK NHS Image Exchange Portal to Cambridge, followed by importing to Mindways QCT Pro.The Mindways QCT Pro SlicePick vertebral fracture assessment tool is used to identify any fractures in the imaged CT volume during the bone density assessment, by applying 6-point morphometry criteria to the synthesised lateral image (upper panels of figure 3). SlicePick works by synthesising anteroposterior and sagittal images from the axial CT slices.Mindways QCT Pro CTXA module is used to measure bone mineral density (BMD) in the left femoral neck (figure 3, middle panes), left total hip region (if coverage is sufficient) and/or lumbar spine (L1-L3 as per International Society for Clinical Densitometry guidelines, lower panes, figure 3).Each individual’s Fracture Risk Assessment (FRAX) fracture risk estimate is then recalculated online, using clinical Risk Factors (RFs) from FRAX and the femoral neck BMD value. Importantly, the ‘previous fracture’ category is switched to ‘yes’ in FRAX if spine imaging revealed any vertebral fracture.The NOGG guidance tool button within FRAX is then used and the pop-up red/green risk charts followed to determine whether treatment is recommended, provided no contraindications exist. In the case of no femoral neck BMD possible (spinal BMD only), FRAX values are reported (without BMD input) and the PHOENIX clinical decision tree for spine BMD is followed to produce the report that is sent to general practitioners (GPs).The clinician-verified report phrases are derived from the PHOENIX clinical decision tree (online supplemental material 2), which is stored within the QCT Pro reporting tool and updated regularly. The report phrases appear (figure 2) on the Hip pdf (CTXA Hip Bone Mineral Densitometry, ‘GP Advice’) analysis and the Spine pdf (Spine 3D QCT Bone Mineral Densitometry ‘GP Advice’). The technicians can select the correct GP advice phrase via drop-down menus when they have the FRAX and BMD results to hand. By selecting the matching patient category in the software, a bespoke template is imported into the pdf of the bone density report incorporating all the measured bone health information and clinical risk factors, based on the National Osteoporosis Guideline recommendations.The final Hip and Spine pdf is signed off electronically by the consultant physician ([name]) via nhs.net email (secure clinical, encrypted) and posted to GPs with a cover letter.Any vertebral fractures overlooked by radiologists on the Radiology Information System (RIS) report are entered in the local radiology discrepancy review process and the original CT report addended accordingly.Responsibility for subsequent investigations including referrals for dual energy X-ray absorptiometry and/or treatment, remain with the GP.A small, cylindrical Mindways model 4 (asynchronous CT calibration phantom) must be scanned at intervals on each CT scanner, including all the various kilovoltage peak energies used clinically, according to a Standard Operating Procedure. This phantom can be posted or taken to radiology departments for quality assurance scanning.

Baseline and 1-year follow-up postal questionnaires are sent to all randomised participants to collect data on quality of life and resource use relevant to bone health for health economic analysis. For non-responders, a telephone interview is attempted aiming to collect the questionnaire data. Patient and clinician/healthcare worker/administrator perspectives of study involvement are explored through semi-structured interviews by telephone. All study data are held securely processed in accordance with the Data Protection Act 2018 and not disclosed to third parties. Manual records will be held securely (eg, in locked filing cabinets). Electronic records will be held on a secure network requiring user ID and password access. Individuals are not identifiable from the REDCAP and JMP (V.15, SAS Institute) spreadsheet results of the trial. The Project Management Team members ([name]) are responsible for the day-to-day running of the study to discuss practical aspects and ensure it is progressing. The Trial Management Group (TMG) comprises the protocol authors and one patient and public involvement (PPI) member. They are responsible for the overall conduct of the study and ensuring the National Institute for Health and Care Research (NIHR) milestones are achieved. Prior to COVID-19, separate PPI meetings were held which enabled those attending to influence the study design.

### Sample size calculations, study power, randomisation method

Our primary intention is to evaluate the technical procedures needed for a definitive trial with fracture incidence (rather than recruitment/retention) as the primary outcome. To help set the target recruitment numbers for the feasibility study, we therefore used the surrogate outcome of osteoporosis treatment rates at 12 months follow-up to permit sufficient power to assess and conduct cross-group comparisons across trial arms within the period of recruitment to the feasibility study. Scenarios for scaling up to a definitive trial are based on previous data.^1 2 9^ Only those participants in the red/amber FRAX group (figure 4A) will be randomised, so the number of invitations needed to reach any recruitment target will also depend on the prevalence of the red/amber FRAX group. In our local preliminary application of the PHOENIX intervention in 1518 patients, the prevalence of red/amber FRAX varied between 30% at age 40 years and 50% at age 95 years (figure 4B), with overall prevalence 40.5% (95% CI 35.7% to 45.5%). There is no published UK data to compare with this but comparable prevalence was reported in a single study in the USA investigating combined bone density and fracture detection in routine CT investigations, where 42.3% (of 571 consecutive patients) were newly detected as having osteoporosis.^1^ A conservative assumption from our preliminary work is that the PHOENIX intervention will identify a further 9.6% of screened patients for treatment and that GPs will act to treat at least half of these, resulting in an expected 4.8% minimum detectable difference. If, in our study, the percentage treated at 12 months in group 2 (active control FRAX-GP arm) matches that observed in the MRC-funded osteoporosis screening Screening in the community to reduce fractures in older people (SCOOP) study^6^ (15.5%), then we would consider that an improvement in percentage treated of 4.8% would be clinically significant. Figure 4C shows the estimated total number of invitees needed to recruit the 375 red/amber risk participants, assuming different response rates and different prevalence estimates. In the scenario of 30% response (similar to SCOOP) combined with 40% prevalence of red/amber FRAX (red line in figure 4D), it would be necessary to invite a total of 3125 participants (or 625 invites per centre) to achieve the recruitment target of 375 randomised participants (75 per centre, figure 4D).

